## Introduction

 Reducing unnecessary psychiatric hospital admissions and length of hospital stay for people with intellectual disability and autistic people has been a focus of English national health policy since the scandal of abuse and neglect of patients at Winterbourne View Hospital in 2011.^1^ The Transforming Care programme was established to improve community health and social care for people with intellectual disability and autistic people and to reduce what had generally been considered to be an over-reliance on inpatient psychiatric services.^2^ A key element of Transforming Care has been the introduction of Care (Education) and Treatment Reviews (C(E)TRs), person-centred review meetings that aim to ensure the right support is provided.^3^ A community C(E)TR should be convened when a person with intellectual disability or an autistic person living in the community is considered at high risk of admission to a psychiatric hospital, either because of mental ill-health or because of an escalation in behaviours that challenge. C(E)TRs are chaired by a health commissioner and include an independent clinical expert and an expert-by-experience, often a family carer of a person with intellectual disability or an autistic person. This panel gathers information from the individual, their families and carers, and professionals, and produces a report and action plan following the C(E)TR with recommendations (eg, input from specialist professionals or health teams, provision of additional care, use of respite services) that can enable the person to remain living safely in the community. Where admission to hospital is considered necessary, the C(E)TR panel will define the purpose of the admission and encourage early discharge planning in order to minimise the length of the hospital stay. Inpatient C(E)TRs are convened at various points of a hospital admission; the current project investigates only C(E)TRs that are held in the community.

Little formal research has been carried out on community C(E)TRs, such as who receives them and when, and how C(E)TRs may influence health service use, including admission to hospital. By understanding the demographic and clinical profile of patients who do, and do not, have a community C(E)TR, it may be possible to develop targeted interventions to improve access to community C(E)TRs and ensure the potential benefits are available to everyone.

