## Methods and analysis

### Study setting

Data will be obtained from the South London and Maudsley (SLaM) NHS Foundation Trust. SLaM is one of the largest providers of secondary mental healthcare in Europe, with a diverse catchment area of approximately 1.3 million people who live in the south London boroughs of Lambeth, Southwark, Lewisham and Croydon. Mental health services provided by SLaM include specialist teams for children and adolescents with mental illness and/or neurodevelopmental conditions, community teams for adults, including specialist teams for those with intellectual disability, and mainstream and specialist inpatient wards across different sites. The Trust has implemented a full EHR since 2006, and the SLaM NIHR Maudsley Biomedical Research Centre Case Register contains the clinical records of >5 00 000 patients.^4 5^ Unless otherwise stated, data will be extracted up to an end date of 31 December 2024. The protocol for this study was finalised in July 2025. Data extraction is anticipated to be complete by September 2025 and data analysis by December 2025.

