### Matching a control group

We will match between one and five controls, who will not have a community C(E)TR, per patient who has a C(E)TR. Eligibility will be a diagnosis of intellectual disability or autism and having received a continuous period of community care within SLaM services for at least a year between 1 January 2015 and 31 December 2023. Matching will be based on age (±3 years), sex (male/female) and diagnosis (intellectual disability with/without autism, or autism without intellectual disability). Controls should be under an active episode of community care and not be an inpatient on the index date of their matched case. They must also have been under SLaM services for a similar total duration of their matched case (±2 years). Matching with replacement will be applied to ensure every case has an appropriate match according to these criteria. A pseudo-index date for each control will be assigned and will be the same as the index date of their matched case.

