##### Stage 1: propensity scores

As the retrospective analysis of EHRs is not a randomised controlled study, we will employ a propensity score weighting technique to adjust for confounders in the data. Propensity scores will balance the C(E)TR and comparison groups on a set of baseline (pre-index date) characteristics.^12^ Certain characteristics may increase the probability of someone receiving a C(E)TR, and we wish to account for these in the outcome (risk of hospitalisation) model. Scores will be calculated by fitting a multivariable logistic regression model with C(E)TR status as the dependent variable.^13^ We will condition on baseline characteristics that are believed to be related to the outcome, risk of hospitalisation, and to the probability of receiving a C(E)TR (confounders), but not those that might lie on the causal pathway from receiving a C(E)TR to being admitted to hospital (mediators), that is, variables that are affected by the intervention itself. The following variables are expected to be included in the propensity score analysis: age, sex, ethnicity, marital status, sexual orientation, deprivation score, relevant diagnosis (intellectual disability with/without autism, or autism without intellectual disability) and pre-existing psychiatric diagnoses (online supplemental table 1).

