#### Time-to-event analysis

Time-to-discharge (length of hospital admission) will be analysed using the Kaplan-Meier estimator.^19^ A Cox’s proportional hazards model will be used to estimate the HR for discharge,^20^ comparing those who received a C(E)TR to those who did not receive a C(E)TR for a follow-up period of 6 months after admission. This analysis will be adjusted for C(E)TR status prior to admission, age at admission, sex, ethnicity and relevant diagnosis at admission (intellectual disability with/without autism, or autism alone). Patients who die within 6 months of admission will be censored at the date of death, and patients who remain in hospital will be censored at the end of the 6 months.

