#### Improvement in clinical and social functioning during hospital admission

Although we expect variation in how frequently HoNOS scores are collected and some missing data, we will attempt to extract HoNOS scores at two time points of a patient’s psychiatric admission: the closest HoNOS score recorded around the admission date (± a maximum of 3 months) and the closest recorded HoNOS score to the discharge date (± a maximum of 3 months). A linear regression model will be carried out with the difference in total HoNOS score as the dependent variable. C(E)TR group will be the main independent variable of interest, with baseline HoNOS included as a covariate. Age, sex and ethnicity will be included as confounders. We want to understand if having a community C(E)TR before hospital admission is associated with greater improvements while in hospital. As variations of HoNOS are applied across different populations, we will carry out this analysis on the version that has the least missing data.

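### Sub-study 2 compares length of stay and HoNOS change with no term for area, so if C(E)TR uptake and discharge speed both vary by borough, the discharge HR is biased; stratifying by borough is a cheap protection

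*Protocol article*

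**What the plan says.** **Exposure and setting.** The Introduction of the protocol article says that "C(E)TRs are chaired by a health commissioner and include an independent clinical expert and an expert-by-experience". Study setting describes a catchment of "people who live in the south London boroughs of Lambeth, Southwark, Lewisham and Croydon", with "mainstream and specialist inpatient wards across different sites".

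**Sub-study 2 (hospital cohort).** Patients with and without a community C(E)TR in the 6 months before admission are compared directly, with no matching or weighting.
- Time-to-event analysis, for the primary outcome of length of stay: "This analysis will be adjusted for C(E)TR status prior to admission, age at admission, sex, ethnicity and relevant diagnosis at admission". C(E)TR status is the exposure, so the adjustment covariates are age, sex, ethnicity and diagnosis.
- Improvement in clinical and social functioning: baseline HoNOS is a covariate, and "Age, sex and ethnicity will be included as confounders".

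**Sub-study 1 (community cohort).**
- Matching a control group: "Matching will be based on age (±3 years), sex (male/female) and diagnosis", plus time under the Trust's services, an active community episode and not being an inpatient on the index date.
- Stage 1: "The following variables are expected to be included in the propensity score analysis: age, sex, ethnicity, marital status, sexual orientation, deprivation score", then diagnosis and pre-existing psychiatric diagnoses. This list is only provisional and points to a supplemental table that is not shown.
- Stage 2: a weighted difference-in-differences (DiD) model, with a post-period logistic regression as fallback.

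No borough, commissioning area, team or site appears in any of these lists as printed.

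**The concern.** By the protocol's own description, a C(E)TR depends on a commissioner as well as on the patient. Its recommendations draw on extra care, respite and specialist input, and when admission goes ahead the panel encourages early discharge planning. Area could therefore plausibly be related both to who gets a C(E)TR and to how soon a patient can leave hospital. It also precedes the exposure, so it is a natural candidate under the rule in Stage 1 of conditioning on variables related to both exposure and outcome.

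Sub-study 2 is the exposed part. Its covariate lists are stated without qualification, they are the only adjustment, and they omit even the deprivation score that sub-study 1 would use. If an area holds more C(E)TRs and also discharges faster (or slower), that difference enters the HR for C(E)TR. The error is systematic and does not shrink with sample size. The replication does not remove it, because the same models would be rerun at the second Trust.

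**Working it through.** The protocol gives no figure to reproduce: no sample size, no C(E)TR count and no borough rates. All borough inputs below are assumptions.

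**1. Sub-study 2, Cox model.**

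Taken from the protocol: four boroughs, stays of at least 14 days, follow-up of 6 months. Assumed: boroughs of equal size, median stay of 60 days beyond day 14 at relative rate 1, censoring at day 182, true C(E)TR HR of 1 within every borough.

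Let p_b be C(E)TR uptake and r_b the relative discharge rate in borough b. At the start of the risk period, a model that ignores borough sees

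HR ≈ [Σ p_b r_b / Σ p_b] ÷ [Σ (1−p_b) r_b / Σ (1−p_b)].

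*Moderate variation:* uptake 5/10/15/20%, rates 0.80/0.93/1.07/1.25.
- C(E)TR group: (0.040 + 0.093 + 0.1605 + 0.250)/0.50 = 0.5435/0.50 = 1.087
- No C(E)TR: (0.760 + 0.837 + 0.9095 + 1.000)/3.50 = 3.5065/3.50 = 1.002
- Ratio 1.085. The simulated Cox HR averages 1.08 to 1.09.
- Rates in reverse order: (0.469/0.50)/(3.581/3.50) = 0.938/1.023 = 0.917. The Cox HR is about 0.92.

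*Strong variation:* uptake 2/5/15/30%, rates 0.7/0.9/1.1/1.4.
- (0.644/0.52)/(3.456/3.48) = 1.238/0.993 = 1.25. The simulated Cox HR averages about 1.27.
- Reversed, the Cox HR is about 0.80.

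Both sets put uptake and discharge rate in perfect rank order, or its exact reverse. Over all 24 ways of pairing the four uptakes with the four rates, the large-sample HR behaves as follows:

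| Assumed set | Range of HR | Median distortion |
|---|---|---|
| Moderate | 0.92 to 1.09 | about 4% |
| Strong | 0.80 to about 1.26 | about 13% |

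False-positive rates with 400 to 800 admissions and perfect alignment are 7 to 12% (moderate) and 33 to 57% (strong). Stratifying by borough gives HR 1.00 and 4 to 5%. If borough is unrelated to discharge, stratifying raises the SE by about 2%.

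*A second layout as a check:* two fast and two slow boroughs, with fast-to-slow discharge HR of 1.25, 1.5 or 2.0.

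| Uptake, fast/slow | HR without borough | HR stratified |
|---|---|---|
| 20%/20% | 1.00, 1.00, 1.00 | 1.00 to 1.01 |
| 20%/10% | 1.04, 1.09, 1.13 | 0.99 to 1.01 |
| 30%/10% | 1.07, 1.13, 1.22 | 0.99 to 1.00 |
| 40%/10% | 1.10, 1.18, 1.31 | 1.00 |

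With equal uptake, or with equal discharge rates, the bias is nil. Both links are needed.

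**2. Sub-study 1.**

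Using the same two-type layout, suppose uptake is 20%/10%. The share living in high-uptake boroughs is 0.2/0.3 = 0.67 among cases and 0.8/1.7 = 0.47 among controls, a gap of 0.196. At 40%/10% the shares are 0.80 and 0.40, a gap of 0.40.
- *DiD, stable area difference in admission risk:* it cancels, so the bias is 0.
- *DiD, high-uptake boroughs with a trend 3 points more favourable:* −0.03 × 0.196 = −0.6 points, up to −0.03 × 0.40 = −1.2 points.
- *Logistic fallback:* admission risk 10% against 15%, uptake 20%/10%, gives 11.7% against 12.6%, OR 0.91. Risk 10% against 20%, uptake 40%/10%, gives 12% against 16%, OR (0.12/0.88)/(0.16/0.84) = 0.72.

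**The case against.** The strongest reply is that neither link is in the document. It says that a commissioner chairs the meeting. It does not say that commissioning is organised by borough, that uptake differs by borough, or that discharge speed does. This stands: the point is about possible confounding of unknown size.

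A reader might go further and infer three things that the document does not support.
- *That the sub-study 1 admission estimate is confounded by borough.* The DiD removes stable area differences. What remains needs local trends that track uptake, or use of the logistic fallback. The propensity list is provisional, refers to a table that is not shown and includes a deprivation score that may carry some area information, so it cannot be said that borough is excluded from that model.
- *That an HR near 1.27 with 33 to 57% false positives is to be expected.* That needs a 15-fold spread in uptake, a two-fold spread in discharge rate and perfect alignment of the two.
- *That controls must be matched within borough.* The number of C(E)TRs is unknown and may be small. Matching already uses age, sex, diagnosis and service duration, and every case is meant to be matched. A further exact criterion would strain that.

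It can also be said that sub-study 2 is worded mainly as a comparison, with causal modelling reserved for sub-study 1. But the abstract states the aim as investigating effects on length of stay, and an adjusted HR will be read that way. Separate replication is a partial check, since a chance borough pattern need not recur.

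Finally, if borough predicts uptake but not outcome, adjusting for it costs precision and can amplify residual confounding. That is fair, and is a reason to report the Cox model both ways.

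**Conclusion.** The point holds for sub-study 2, as a cheap improvement. The Cox and HoNOS models are fixed with no area term and no other protection, for an exposure run through commissioners in a four-borough Trust. If uptake and discharge speed both vary by area, the primary discharge HR is biased in a direction that cannot be known in advance. Under the assumed moderate variation and no true effect it would lie between about 0.92 and 1.09. Larger distortion needs strong variation with the two patterns aligned. If either link is absent, there is no bias.

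For sub-study 1 the point is secondary. It matters mainly for the logistic fallback and for differing local trends.

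The document does not establish that borough confounding is present, and every magnitude here rests on assumed borough rates.

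**What to change.** 1. **Time-to-event analysis:** stratify the Cox model by borough of residence at admission, or by responsible commissioning area if the extract holds it. Report the unstratified HR beside it.
2. **HoNOS regression:** add borough as a covariate.
3. **Replication Trust:** use its local areas in the same way.
4. **Sub-study 1:** name borough as a candidate in the propensity model. Do not require within-borough matching.
5. **Descriptives:** tabulate C(E)TR uptake and length of stay by borough, so that a reader can see whether either link exists.

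Cost: four strata in the Cox model or three extra parameters in the regressions. The SE is slightly larger if borough is irrelevant: about 2% in the assumed settings of 400 to 800 admissions and equal boroughs, and possibly more with few C(E)TRs or very unequal boroughs. Area of residence must also be available in the de-identified extract. The planned deprivation score suggests that area information exists in the source record, but the protocol does not say that borough itself will be released, so this should be confirmed before the wording is changed.

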### Multiple C(E)TRs

Community C(E)TRs of >6 months apart for the same patient will be treated as separate events. As community C(E)TRs require substantial planning and organisation, we expect few to take place within 6 months of a previous C(E)TR; however, if this occurs, the earlier C(E)TR date will be used as the index date and a second C(E)TR within the 6 month timeframe will be excluded from analysis.

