### Index date

The index date will be defined as the date on which a community C(E)TR was held.

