### Outcome

The primary outcome will be psychiatric hospital admission (treated as a binary variable) at any time within 6 months after the index date (online supplemental table 2).

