#### Causal effect of community C(E)TRs on risk of hospitalisation

A two-stage framework will be applied to evaluate the causal effect of having a community C(E)TR on hospital inpatient prevalence after the C(E)TR; propensity score weighting (propensity model) and a difference-in-differences (DiD) analysis (outcome model). We will compare changes from the 6 months before the index date and the 6 months after the index date, between people with intellectual disability and autistic people who had a C(E)TR and those who did not. The outcome will be whether a person has a psychiatric inpatient admission at any time in the 6 months after the index date.

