### Sensitivity analyses

Sensitivity analyses will be carried out on the causal framework to probe the robustness of the applied model. During the C(E)TR identification process, we will identify patients for whom a community C(E)TR was suggested, where there was no evidence that a C(E)TR did in fact occur. These are to be included in the pool of control patients in our main analysis. Exploratory sensitivity analyses will: (1) Re-assign these patients to the C(E)TR group, and use the date in the record when a C(E)TR was suggested (or soon thereafter) as the index date and/or (2) Directly compare the main C(E)TR group with the ‘C(E)TR suggested’ group.

Some patients may have multiple community C(E)TRs while under follow-up. These will be treated as separate events in the main analysis (if the C(E)TRs are at least 6 months apart). Patients who have multiple C(E)TRs may have a different profile of baseline characteristics than those who receive only one. This may lead to preintervention differences in the C(E)TR versus no C(E)TR groups that cannot be sufficiently controlled for using the propensity scoring method. A sensitivity analysis will be performed on the subgroup of patients who only had one C(E)TR (vs no C(E)TR), improving sensitivity to the causal effect of a single C(E)TR.

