#### Analysis of a 12-month horizon

We will re-run the analyses for both sub-studies across a 12-month horizon, to extend the results of the reported 6-month horizon and to capture potential impacts of community C(E)TRs across a longer time-frame.

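### Repeat C(E)TRs 6 to 12 months apart enter the main difference-in-differences with overlapping windows, so the second event's baseline is partly post-treatment

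*Protocol article*

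**What the plan says.** All places are in the protocol article, sub-study 1 unless stated.

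- **Index date:** "The index date will be defined as the date on which a community C(E)TR was held". Every included C(E)TR therefore has its own windows.
- **Outcome:** "psychiatric hospital admission (treated as a binary variable) at any time within 6 months after the index date".
- **Causal effect of community C(E)TRs on risk of hospitalisation:** "We will compare changes from the 6 months before the index date and the 6 months after the index date". The Stage 2 section takes the effect in the treated as the estimand and relies on before-and-after data from the same patients to strengthen the causal claim.
- **Multiple C(E)TRs:** "Community C(E)TRs of >6 months apart for the same patient will be treated as separate events". For closer repeats, "a second C(E)TR within the 6 month timeframe will be excluded from analysis".
- **Sensitivity analyses:** this section confirms that repeats belong to the main analysis, but words the limit as a gap of 6 months or more, where Multiple C(E)TRs has strictly more than 6. It then adds: "A sensitivity analysis will be performed on the subgroup of patients who only had one C(E)TR (vs no C(E)TR". The reason given is that patients with several C(E)TRs may differ at baseline. Overlap is not mentioned.
- **Analysis of a 12-month horizon:** "We will re-run the analyses for both sub-studies across a 12-month horizon". No new spacing rule is stated.

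**The concern.** A difference-in-differences analysis needs a before-period that the intervention has not touched. The spacing rule equals the length of one window, but each event occupies two windows, one on each side of its index date. Two events 6 to 12 months apart therefore use some of the same calendar months twice: as follow-up for the first and as baseline for the second.

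This has two consequences for the primary causal estimate. The baseline of the second event partly reflects whatever the first C(E)TR did. And an admission in the shared months, which is a primary outcome event for the first C(E)TR, is subtracted again as baseline for the second.

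The one planned analysis that avoids the overlap has its own weakness. Whether a patient only ever has one C(E)TR is known only after the index date, so that subgroup leaves out people whose later course led to another review.

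**Working it through.** The article gives no sample size, admission rate or share of repeats, so there is no figure of its own to reproduce. The window arithmetic follows from the stated rules. The size calculation rests on assumptions, marked as such.

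**1. Overlap in the main analysis (6-month windows).** Put the first C(E)TR at month 0 and the second at month g. The first after-window is 0 to 6 and the second before-window is g−6 to g. For g from 6 to 12 they share months g−6 to 6, that is 12−g months.

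| Gap g (months) | Shared months | Share of window |
|---|---|---|
| just over 6 | about 6 | about 100% |
| 7 | 5 | 83% |
| 8 | 4 | 67% |
| 9 | 3 | 50% |
| 10 | 2 | 33% |
| 11 | 1 | 17% |
| 12 or more | 0 | 0% |

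**2. What happens to one admission.** Take g=9, so the shared months are 3 to 6, and write (pre1, post1, pre2, post2).
- Admission at month 4: (0, 1, 1, 0). Sum of changes = (1−0)+(0−1) = 0. It cancels.
- Admission at month 1: (0, 1, 0, 0). Sum of changes = +1. It does not cancel.

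Only admissions in the last 12−g months of the first after-window are affected.

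**3. Size if repeats are unrelated to admission (assumptions).** Assume a 6-month admission risk of 20%, flat controls, equal event weights, gaps uniform over 6 to 12 months, and an effect that multiplies the admission rate by r for 6 months. The monthly rate is λ = −ln(0.8)/6 = 0.0372.
- For r=0.5 the after-risk is 1−0.8^0.5 = 0.1056, so the true difference is 0.1056−0.2000 = −0.0944.
- Second baseline: with u = g−6, the mean of 1−exp(−λ[0.5(6−u)+u]) over u from 0 to 6 is 0.1537. Second events alone give 0.1056−0.1537 = −0.0481.
- Pooled estimate = (−0.0944 + s×−0.0481)/(1+s), where s is the share of treated patients with such a repeat: −0.090 at s=10%, −0.084 at 30%, −0.079 at 50%.
- For r=1.5 the true difference is +0.0845 and second events alone give +0.0414. Pooled: +0.081, +0.075 and +0.070.

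The estimate moves towards zero in both directions, by about 0.4 to 1.0 percentage points at 10% to 30% repeats.

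**4. Size if an admission prompts the next C(E)TR (further assumption).** Keep the same set-up with no true effect (r=1). Let the probability of a repeat be 10% without an admission in the first after-window, and q with one.
- q=30%: repeat share = 0.2×0.3+0.8×0.1 = 0.14. The mean of exp(−λu) is 0.2/(6λ) = 0.896. Second baseline = 1−0.8×(0.3−0.2×0.896)/0.14 = 0.310. Second events give 0.200−0.310 = −0.110. Pooled = 0.14×(−0.110)/1.14 = −0.014.
- q=50%: repeat share 0.18, second baseline 0.371, second events −0.171, pooled 0.18×(−0.171)/1.18 = −0.026.
- q=10% (no link): second baseline 0.200 and no bias.

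First events alone give zero in all three cases.

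**5. The 12-month horizon.** With 12-month windows and the same spacing rule, gaps of 12 to 24 months share 24−g months: 9 at g=15, 6 at g=18, 0 at g=24. For gaps under 12 months the second C(E)TR lies inside the first's follow-up. At g=9, months 0 to 9 are both follow-up for the first event and baseline for the second, and months 9 to 12 are follow-up for both.

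**The case against.** **Partly handled.** The analysis of patients with only one C(E)TR contains no overlap, and the 12-month run is an extension. Both points are correct. But the sensitivity analysis leaves the primary estimate as it is, and it is selected on later events, so a difference between the two results could not be put down to overlap.

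**Not every admission cancels.** This stands. Cancellation is limited to the shared months and is exact only for an equally weighted linear model. With other weights it is approximate. The logistic fallback in Stage 2 has no pre-period term, so nothing cancels there.

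**Direction.** A reader might infer that the overlap favours C(E)TRs. The documents do not establish this. With repeats unrelated to admission, a true benefit is understated. Apparent benefit needs the assumption that admissions prompt repeats. That is plausible, since the Introduction says C(E)TRs are convened for people at high risk of admission, but no rate is given. Selection on a raised baseline could also affect first C(E)TRs and widely spaced repeats, and spacing would not remove it there.

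**Size.** A reader might multiply an assumed 10–30% of repeats by an assumed 20–40% with a shared-month admission and read the resulting 2 to 12 percentage points as bias. That product is a gross count. A clean baseline would contain admissions too, and only the excess biases the result.

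**Standard errors.** A reader might infer inflated type I error from repeat events and from reused controls ("Matching with replacement will be applied to ensure every case has an appropriate match"). The article does not support a figure. Shared months push a patient's successive changes in opposite directions (+1 then −1 in the example above), so the usual positive-correlation design effect does not carry over to this model. Variance estimation may also be set out in a fuller plan.

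**Conclusion.** The point holds as a flaw in a stated rule. For repeats 6 to 12 months apart, the main difference-in-differences uses a baseline that is partly post-treatment, and nothing in the article corrects it. The overlap of 12−g months needs no assumption.

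The effect on the estimate does depend on assumptions. It is roughly 0.4 to 1.0 percentage points towards no effect at 10–30% repeats that are unrelated to admission. It is roughly 1.4 to 2.6 points towards apparent benefit if an admission raises the chance of a repeat from 10% to 30–50%. Both figures assume a 20% six-month admission risk. The article says that even the number of C(E)TR recipients is unknown and expects few repeats within 6 months, but it gives no share for 6 to 12 months. If such repeats are few, the bias is small. The rule is still worth correcting before analysis, because it bears on the primary causal estimate and the remedy uses dates already being extracted.

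**What to change.** 1. In the primary difference-in-differences, use each patient's first eligible community C(E)TR. Alternatively, keep a repeat only when it is at least 12 months after the previous included event, and drop the later one otherwise.
2. For the 12-month horizon, apply the same first-event rule, or a spacing of at least 24 months.
3. Replace the subgroup with only one C(E)TR by an analysis of the first C(E)TR for everyone, whatever follows. If first events are already primary, all adequately spaced events can serve as the sensitivity analysis.
4. Make the Multiple C(E)TRs and Sensitivity analyses sections state the same limit.
5. Report the number of repeats by gap, so that readers can judge how much overlap was at stake.
6. Where repeat events or reused controls remain, cluster standard errors by patient, as a supporting measure.

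**Cost:** a date filter and a few lines of text. Some repeat events leave the primary analysis, which loses some precision. Using first events only narrows the estimand to first C(E)TRs, and the text should say so. The spacing option keeps more events, but a dropped C(E)TR can still fall inside a later baseline: with events at months 0, 8 and 14, the second is dropped and the third has a before-window of months 8 to 14. First events only avoids this.
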